### **Inclusion Criteria**

1. Gestational age 26-32 weeks at birth, as determined by Dubowitz/Ballad examination and/or obstetric ultrasound done at less than 15 weeks.
2. At least 28 weeks post menstrual age at the time of enrollment.

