### **Randomization**

A stratified blocked randomization technique will be used. The subjects will be randomized to the **Experimental Group** or the **Control Group** and stratified into three groups based on their GA:

- 26-28 and 6/7 weeks gestation,
- 29-30 and 6/7 weeks gestation,
- 31-32 and 6/7 weeks gestation. (Pilot Study – Discontinued Spring 2013)

A blocked randomization technique will be used to ensure approximately equal number of subjects are in each group. The randomization will be generated by SAS v. 9.1 statistical software program. Just prior to randomization, the inclusion and exclusion criteria will be reviewed for each candidate.

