## **STATISTICAL ANALYSIS**

### **Sample Size Calculation**

The principal study subjects are infants born between 26 and 30 weeks gestation. The sample size was calculated based on the alternative hypothesis that the preterm infants born before 31 weeks gestation in the experimental group will transition initiation of oral feeds to attaining full oral feeds 5 days earlier than

the control group. Data from Simpson et al, (2002) demonstrate that infants who underwent a standard protocol for early oral feeding advance transitioned to the full oral feeds at  $23 \pm 12$  (Mean  $\pm$  SD) days. All subjects will be followed until they attain full oral feeds. Therefore it is expected that the time to full oral feeds will be available for all or nearly all subjects (i.e. there will be little or no censoring of event times). Since the time to full oral feeds may be right skewed, the Wilcoxon Rank Sum test will be used as the primary analysis. We consider 5 days to be a clinically significant difference between the control and the experimental group. Thus, 105 infants in each group of a two-sided alpha of 0.05 yield 80% power ( $\beta=0.2$ ) to detect a 5 day difference in the time to reach full feeds.

The percent of subjects with censored times are those leaving the trial prior to attainment of full oral feeds. Censored data will be assessed in a fully blinded way when 75% of the target sample size has completed the protocol. If rate of censoring is higher than 10% at this time, the planned use of the Wilcoxon Rank sum test will no longer be considered appropriate, and a log-rank test will become the primary analysis. Since the log-rank test has lower power, the sample size will need to increase to 160 subjects per group to achieve 80% power to detect a 5-day difference in median time to full oral feeds.

The infants between 31 and 32 weeks of gestation may attain full oral feeds much sooner compared to the younger gestation; therefore the effect size may vary considerably in this group of preterm infants. We will include the 25 subjects per group born between 31 and 32 weeks gestation to obtain pilot data on their effect size in order to calculate the sample size for this group, but the primary analysis will not include these subjects.

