### **Data Analysis**

The primary outcome of the study is the time to attain full oral feeds. All subjects will be followed until they attain full oral feeds. Wilcoxon Rank Sum test will be used to test for a difference between the two groups. A secondary, supportive analysis will be performed using the log-rank test, with the understanding that this test will likely be underpowered. As mentioned in the sample size section, in the event that the rate of censoring is higher than the 10% of evaluable subjects expected, the Wilcoxon Rank Sum test will not be considered appropriate and the log-rank test will be elevated to the primary analysis method.

The null hypothesis is that there will be no difference in the median times to full oral feeds in the experimental group versus the control group, this will be tested using a 0.05 two-sided significance level, with the following hypotheses:

$$H_0 : M_{NT} = M_C$$

$$H_a : M_{NT} \neq M_C$$

Where  $M_{NT}$  and  $M_c$  refer to the population medians in the NTrainer System® group and the control group, respectively.

The time to event will be measured as the number of days from the initiation of oral feedings to full oral feeding. Kaplan-Meier survival curves will be produced to illustrate the time of attainment of full oral feeds in the two groups. As a supportive analysis, a Cox proportional hazards regression model will be used to test for a difference in the time to attain full oral feeds between the two groups, while controlling for age group (26-27, 27-28, 29-30 and 31-32 weeks post menstrual age) and the presence of co morbid conditions that interrupt the feeding schedule.

Exploratory subgroup analyses of the primary outcome in each of the different gestational age groups (26-27, 27-28, 29-30 and 31-32 weeks post menstrual age) will be performed to evaluate for any difference in

the effect of the NTraining® at different gestational ages, and within groups having and not having co morbid conditions that interrupt the feeding schedule.

The secondary outcome variables of time from the initiation of the NTrainer System® training to first and fourth successful oral feeds will analyzed in the same manner as the primary outcome variable.

The rate of milk transfer at the time of full oral feeds will be compared between groups using an independent t-test. We will also compare the NNS parameters after the completion of NTrainer System® and at the time of full oral feeds using *t* tests.

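### The age groups fixed for the supportive Cox model and the exploratory subgroups overlap at 27 weeks, carry the wrong age label, and bring the excluded 31-32 week pilot group into the Cox model

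*Protocol*

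**What the plan says.** The Data Analysis section of the protocol adds a supportive Cox model for the primary outcome, "controlling for age group (26-27, 27-28, 29-30 and 31-32 weeks post menstrual age". The exploratory subgroup analyses of that outcome are then to be done "in each of the different gestational age groups (26-27, 27-28, 29-30 and 31-32 weeks post menstrual age". The bands are identical in the two sentences, so neither corrects the other.

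The Randomization section defines age differently. Infants are "stratified into three groups based on their GA": "26-28 and 6/7 weeks gestation", "29-30 and 6/7 weeks gestation", and a third stratum running to 32 6/7 weeks that is marked as a pilot discontinued in spring 2013.

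The Sample Size Calculation section plans 25 infants per group for that pilot. It gives as the reason for separating them that their effect size may differ considerably, and closes "but the primary analysis will not include these subjects".

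Inclusion Criteria require "At least 28 weeks post menstrual age at the time of enrollment". Later in Data Analysis, the Cochran-Mantel-Haenszel (CMH) tests for neonatal morbidity and breastfeeding ability also adjust for age group, without printing any bands.

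**The concern.** A factor in a Cox model, or a set of subgroups, needs groups that are mutually exclusive and cover everyone analysed. These bands do not. Whoever codes them must move infants to one side of a boundary or drop some, and the protocol gives no rule for that choice. If the choice is made after results are seen, it becomes a post hoc decision.

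Two further faults sit in the same text. The age scale named is not the one used for randomisation. And a model meant to support the primary result lists a group that the primary result excludes. The stated reason for the exclusion is that the treatment effect may differ there. A main-effect term for age adjusts for different baseline speeds to full feeding. It does nothing about a different treatment effect, so pooling these infants works against the protocol's own reasoning.

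**Working it through.** **1. Do the bands partition the eligible range?** Inputs: the four bands from Data Analysis, and gestational ages 26 0/7 to 32 6/7 weeks from Randomization, which is 7 weeks × 7 days = 49 days. For each day, count how many bands contain it.

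| Reading of a band lo-hi | Days in one band | Days in two bands | Days in none |
|---|---|---|---|
| Completed weeks, lo 0/7 to hi 6/7 (as in Randomization) | 42 | 7 (27 0/7 to 27 6/7) | 0 |
| Half-open, lo 0/7 to just below hi 0/7 | 28 | 0 | 21 (all of weeks 28, 30, 32) |
| Closed, lo 0/7 to hi 0/7 | 30 | 1 (27 0/7) | 18 (days 1 to 6 of weeks 28, 30, 32) |

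Each row sums to 49. No reading puts every infant in exactly one group. In the primary range alone (26 0/7 to 30 6/7, 5 × 7 = 35 days) the result is the same in kind: 7 days double-classed under completed weeks, or 14 unassigned under half-open intervals (weeks 28 and 30).

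**2. Which age is meant?** Postmenstrual age at birth equals gestational age, so the label is harmless only if birth is the reference point, and the text does not say so. Taken at enrolment, the 28-week minimum empties the 26-27 band. Taken at the start of intervention, which the NTrainerRT Therapy/Intervention section places no earlier than 30 weeks postmenstrual age, the 27-28 band is empty as well. The subgroup sentence mixes both terms: "each of the different gestational age groups (26-27, 27-28, 29-30 and 31-32 weeks post menstrual age".

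**3. How many pilot infants could enter the Cox model?** Inputs from Sample Size Calculation: 105 per group in the primary set and 25 per group in the pilot.

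- Primary: 2 × 105 = 210. Pilot: 2 × 25 = 50.
- Share: 50 / (210 + 50) = 50/260 = 19.2%.
- If the blinded censoring check raises the primary set to 160 per group: 50 / (320 + 50) = 50/370 = 13.5%.

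Both are ceilings, because they assume the pilot filled. The protocol says the stratum was discontinued and does not give the number enrolled.

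**4. Does the main calculation depend on the bands?** The inputs to the 105 per group are a 5-day difference, an SD of 12 days, two-sided alpha 0.05 and 80% power. The two-sample formula gives 2 × (12 × (1.960 + 0.842) / 5)² = 90.4. Dividing by 0.864, the lower-bound efficiency of the Wilcoxon test (my assumption; the protocol does not state it), gives 104.7, or 105. No age band enters.

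**The case against.** The best defence is that nothing decisive rests on these bands. The Wilcoxon test and the fallback log-rank test are stated without age adjustment, and the protocol itself calls the Cox model supportive and the subgroups exploratory. The postmenstrual label is probably a slip, since the subgroup sentence speaks of gestational age. All of this stands, and it lowers the severity. It does not rescue the bands: the protocol prints them, they fail under every reading, and an analysis plan that is not shown could only depart from them.

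Some stronger inferences are tempting but not supported:

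- *The 27-28 band is nearly empty on a postmenstrual-age reading.* At enrolment, any infant born by 28 6/7 weeks could be enrolled during week 28, so that band could be large. Nor does the text say that age is taken at enrolment.
- *The bands abandon the randomisation strata.* The 29-30 and 31-32 bands match. Only the youngest stratum is split, and a finer split without overlap would still carry the strata.
- *Listing 31-32 weeks among the subgroups is an error.* A separate estimate there is what the pilot aim in the Hypothesis section asks for, and stopping the stratum does not remove infants already enrolled. The problem is confined to the Cox model.
- *The CMH tests are wrong.* They name no bands and could mean the randomisation strata. That they use the faulty bands is likely, since no other definition appears in the analysis section, but it is not stated.
- *The eligibility range must be rewritten.* That is a separate matter.

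**Conclusion.** The point holds, with moderate severity. The age grouping in Data Analysis cannot be applied as written: 7 of 49 eligible gestational days fall in two groups under the protocol's own completed-week convention, and 18 to 21 days fall in at most no group under the interval readings, with 27 0/7 still counted twice if both limits are included. The age label contradicts both the subgroup sentence and the stratification. The Cox model lists a group that the primary analysis excludes, amounting to at most 19% of its sample, on the assumption of a full pilot and 210 primary infants.

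A reader might infer that the trial's main result is compromised. It is not: the primary test, its fallback and the sample size do not use these bands. What is affected is the supportive Cox model and the subgroups, together with the CMH comparisons if they share the definition.

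**What to change.** In Data Analysis:

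1. Define age group once, as gestational age at birth in the randomisation strata: 26 0/7 to 28 6/7 and 29 0/7 to 30 6/7 weeks. Use that definition in both the Cox and the subgroup sentences, and delete the postmenstrual-age label.
2. State that the supportive Cox model is fitted in the primary population, 26 0/7 to 30 6/7 weeks.
3. Report the 31-32 week pilot infants as a separate exploratory estimate.
4. State that age group in the CMH tests means the same gestational-age strata.

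This is a text correction. It needs no new data and changes no sample-size figure. It should be made before unblinding, so that the grouping is not chosen with results in view.

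### The subgroup analyses are meant to show whether the device's effect differs by gestational age or comorbidity, but no planned analysis compares the effect between groups

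*Protocol*

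**What the plan says.** The Data Analysis section of the protocol plans "Exploratory subgroup analyses of the primary outcome in each of the different gestational age groups". The same sentence gives the purpose: to look for any difference in "the effect of the NTraining® at different gestational ages, and within groups having and not having co morbid conditions" that interrupt feeding. It names no treatment-by-group term and no contrast between groups.

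The other analyses that use these factors only adjust for them. The supportive Cox model controls for age group and comorbidity. The Cochran-Mantel-Haenszel tests of the binary outcomes control for age group.

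For the primary outcome as a whole, "the Wilcoxon Rank Sum test will be used as the primary analysis", at a two-sided 0.05 level. The Randomization section has two strata in the primary population, "26-28 and 6/7 weeks gestation" and "29-30 and 6/7 weeks gestation", plus a 31-32 week pilot stratum marked as discontinued. The protocol gives no expected stratum sizes.

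**The concern.** Whether the effect differs between groups is a question about a contrast of two effects. A separate analysis in each group asks something else: whether there is an effect in that group, judged on a fraction of the sample. A trial with about 80% power overall has far less in each part, so one group can easily reach significance while another does not, even when the true effect is identical.

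At stake is a statement about who benefits. Randomisation is stratified by gestational age, so results by stratum are likely to be reported. If they are compared by their p-values, chance alone could suggest that the device helps only the younger or only the older infants. The subgroups with and without comorbid conditions have the same weakness. It would remain even if every group were perfectly defined.

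**Working it through.** **Inputs from the protocol.** Sample Size Calculation: "105 infants in each group of a two-sided alpha of 0.05 yield 80% power"; "We consider 5 days to be a clinically significant difference between the control and the experimental group"; 23 ± 12 days (mean ± SD); Wilcoxon rank sum test; 160 per group with a log-rank test if censoring exceeds 10%; 25 per group in the 31-32 week pilot. Randomization: two primary-population strata, arms approximately equal.

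**Assumptions.** The true effect is 5 days in every group. The two strata are equal in size (52.5 per arm on average), with other splits shown below. A group counts as positive if p < 0.05 in that group.

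**1. The protocol's own figure.** For a t-test, n = 2(1.96 + 0.8416)² × 12²/5² = 90.4, so 91 per arm. Dividing by the lower-bound Wilcoxon efficiency of 0.864 gives 104.7 to 105.3, which matches 105. Power at 105 is then 80.1%. Dividing 91 by 3/π, the efficiency for normal data, gives 95.3, which does not match.

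**2. Power in one stratum.** SE = 12 × √(2/52.5) = 2.342 days, and 5/2.342 = 2.135. For a t-test, power = Φ(2.135 − 1.96) = 57%. Multiplying 2.135 by the square root of the efficiency gives 55% (3/π) or 51% (0.864).

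**3. Chance that exactly one stratum is significant,** p1(1 − p2) + p2(1 − p1):

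| Setting | Exactly one significant |
|---|---|
| Equal strata, 105 per arm, t-test / 3/π / 0.864 | 49.0% / 49.5% / 50.0% |
| Splits from 40:60 to 20:80, 105 per arm | 51% to 62% |
| Simulated Wilcoxon, normal data, 5-day shift | 49% |
| Simulated Wilcoxon, gamma data, 5-day shift | 46% |
| Simulated Wilcoxon, lognormal data, 5-day shift | 40% |
| Simulated Wilcoxon, gamma data, effect proportional (18/23), several splits | 47% to 53% |
| Equal strata, 160 per arm, t-test or 3/π | 38% to 39% |

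Simulations used 4,000 trials per setting. The last row uses t-test and Wilcoxon power, not the log-rank test that would apply at 160 per arm.

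The 50% does not depend on the choice of test. Any test with 80% power overall has a standardised effect of 2.80. In each half it is 2.80/√2 = 1.98, so power is Φ(1.98 − 1.96) = 51%, and 2 × 0.51 × 0.49 = 50%. Taking at face value the protocol's claim of 80% log-rank power at 160 per group gives the same answer.

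**4. More bands, as in the Data Analysis section.** It lists four bands, which overlap. Treating the primary population as three equal, non-overlapping bands of 35 per arm, power per band is 41% (t-test) or 40% (3/π). Mixed verdicts have probability 1 − p³ − (1 − p)³ = 73% or 72% (simulated 71%). Adding a 25-per-arm pilot band raises this to 83% to 84%. Exactly one band is significant in 43% with three bands and 36% to 37% with four.

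**5. A direct comparison.** With equal strata, a z-test of the difference between the two stratum-specific mean differences in days rejected in 4.5% to 5.5% of simulated trials with a uniform shift. Its SE is 2.342 × √2 = 3.31 days. For a 5-day difference in effect, 5/3.31 = 1.51 and power is about 33%. For 80% power the difference must be 2.80 × 3.31 = 9.3 days.

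**The case against.** The strongest reply is that the protocol sets no decision rule. The sentence names no subgroup test or subgroup alpha and does not say that p-values will be compared. The 0.05 level is attached to the overall hypothesis. Showing effects by stratum is a normal first step and fits well with estimates, intervals and an interaction term, which an analysis plan not at hand might add. This stands in part. A reader might infer that the protocol intends to declare benefit in whichever stratum reaches significance; the text does not say so, and the percentages above apply only if the results are read that way. It remains that one sentence pairs a question about differences with separate analyses inside groups, and nothing else in the protocol supplies the comparison. That goes beyond detail left for later.

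A second reply is that the 50% belongs to the two randomisation strata, not to the bands listed in the Data Analysis section, and that stratum sizes are unknown. This is correct, so the figure needs its conditions and range. More bands lower the chance that exactly one is significant, but make mixed verdicts more frequent.

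A reader might also take the Sample Size Calculation section to expect different effects in the two primary strata. Its remark that the effect size may vary concerns only the 31-32 week infants, who are outside the primary analysis.

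Finally, the analyses are labelled exploratory. That limits the consequence but does not make the method answer its question.

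**Conclusion.** The point holds as a moderate one. The protocol wants to know whether the effect differs by gestational age and comorbidity, and plans no analysis that compares effects.

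If the separate results are read by significance, a uniform 5-day effect gives exactly one significant stratum in about 50% of trials. This assumes two equal strata, 105 per arm and SD 12. The range is about 38% to 62% over other splits, skewed data and 160 per arm. With three or four bands, verdicts are mixed in about 71% to 84%. A direct test of a difference in days gives a false difference in about 5%.

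The documents do not support saying that half of such trials would produce a false age-specific claim, because no such reading rule is stated. The primary conclusion is unaffected.

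**What to change.** Amend the subgroup sentence in Data Analysis along these lines:

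> Difference in treatment effect by gestational-age randomisation stratum will be assessed primarily by the between-stratum difference in treatment effect in days, with its 95% confidence interval and interaction test. A treatment-by-stratum term in the Cox model is supportive only. Stratum-specific effects will be shown as estimates with 95% confidence intervals. No claim restricted to one age group will be based on within-group p-values. Any comorbidity subgroups that are retained will be handled in the same way.

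The contrast in days leads because the effect of interest is stated in days and the 5% error rate was checked on that scale. The Cox term works on the hazard-ratio scale, where a uniform shift in days need not be a uniform effect. In a simulation of 1,000 trials with 52 per arm per stratum, assumed stratum means of 26-27 and 19-20 days, SDs of 14 and 8-9, and a true 5-day shift in both strata, the Cox interaction rejected in about 8% to 10%, against about 5% for the contrast in days.

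The cost is a few sentences, one contrast and one model term, with no new data or infants. The downside is low power: about 33% for a 5-day difference in effect, and about 9.3 days needed for 80%. A non-significant interaction is therefore not evidence of equal effects, and the confidence interval should carry the interpretation.

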## **HYPOTHESIS**

The **primary aim** of this study is to test the hypotheses:

The *primary hypothesis* is that the preterm infants (26 to 30 weeks gestational age) who undergo the NTrainer System® training will transition to full oral feeds faster than the control group (i.e. the study group will be superior to the control).

The *secondary hypothesis* is that the infants in the NTrainer System® experimental group will have improved NNS parameters after completion of NTrainer System® training, will transition the first 100% oral feed, 100% oral feeds 4 times per day and improved growth at the time of full oral feeds and at the time of discharge.

The **secondary aim** of this study is to collect data on infants born after 31-32 weeks gestation who undergo the NTrainer System® training as pilot study to determine the effect size for future studies involving preterm infants.

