### **NeoSuckRT® Assessment**

The development of nipple compression pressure dynamics associated with the NNS will be monitored using the NeoSuckRT® program. This assessment of NNS will occur 15 minutes prior to a gavage or oral feed that is not assigned to an NTrainer System® intervention. A 3-minute digital record of NNS activity will be sampled and the digitized record of NNS behavior will be subjected to quantitative indexing of NNS amplitudes and cycle periods within burst, using a specially designed NNS waveform discrimination algorithm. After the NeoSuckRT® procedure is completed, the infant will be fed by the attending nurse. If the baby is able to feed by mouth, the investigator may observe the feeding. Speech pathology, physical/occupational therapists, research coordinators, or staff nursing may perform the assessments.

All infants enrolled in the study (**experimental group** and **control group**) will first start on the NeoSuckRT® program. They will have at least two assessments including clinical assessment by the nursing staff or research staff and assessment using the NeoSuckRT® program prior to the study intervention. The NeoSuckRT® assessment will be done at least three times a week before, during and after the study intervention is completed until the infant reaches the primary outcome.

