### **Secondary Outcome Measures**

1. Feeding parameters:
  - a. The time (days) from the initiation of the NTrainer System® training to the first successful and four successful oral feeds in 24 hours.
  - b. Rate of milk transfer (ml/minute) at the time of full oral feeds—no gavage feeding.
2. Development of NNS parameters assessed by the NeoSuckRT® program
  - a. STI – STI NNS Index
  - b. Bursts/Minute
  - c. Events/Burst
  - d. NNS Events/Minute
  - e. % NNN Events
  - f. Total Events/Minute
3. Growth velocity from the initiation of NTrainer System® training to discharge.
  - a. Weight Gain (grams per kilogram per day)
  - b. Head Growth (centimeters per week). Occipitofrontal circumference - place measuring tape around the front of the head, above the brow and the occipital area. The measuring tape should be above the ears.
4. Length of hospital stay (days).
5. Necrotizing enterocolitis, aspiration pneumonia, and death events.
6. Ability to breast feed prior to discharge based on LATCH score.

During the study, adverse events will be monitored to ensure that the rate of reported events does not exceed the expected rate. Also, concomitant medications, concurrent procedures, therapies and protocol deviations will be documented.

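### The six NNS parameters are t-tested without baseline or GA stratum, and the extra comparison at full oral feeds falls at a time that treatment is meant to change

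*Protocol*

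**What the plan says.** All references are to the protocol.

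- **Data Analysis** fixes the method and two time points: "We will also compare the NNS parameters after the completion of NTrainer System" and "at the time of full oral feeds using *t* tests". No baseline, age or stratum term is named. The Cox model in the same section and the CMH tests for the binary outcomes do control for age group.
- **Secondary Outcome Measures** lists six parameters under "Development of NNS parameters assessed by the NeoSuckRT® program".
- **Hypothesis** ties the expected benefit to one time point: infants in the experimental group "will have improved NNS parameters after completion of NTrainer System® training".
- **NeoSuckRT Assessment** (under the intervention heading) covers both arms before treatment: "They will have at least two assessments including clinical assessment by the nursing staff or research staff and assessment using the NeoSuckRT® program". It then sets how often recordings are made, and ends them once the primary endpoint is met: "assessment will be done at least three times a week before, during and after the study intervention is completed until the infant reaches the primary".
- **Randomization** stratifies by GA at birth.
- **Sample Size Calculation** plans on experimental infants who "will transition initiation of oral feeds to attaining full oral feeds 5 days earlier than" controls.
- **Background** treats sucking as a marker of neurobehavioural maturation and gives no rate of change for any NNS parameter.

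**The concern.** There are two separate issues.

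**Precision.** A pre-treatment value of the outcome and the stratification factor are normally the two most useful covariates for a continuous endpoint. Both are available here, and the stated test uses neither. The endpoint is described as development, which implies a starting point, yet the text does not bring that starting point into the comparison.

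**Timing.** Reaching full oral feeds is the primary event. If the device works, treated infants arrive there sooner. NNS measured at that moment is then measured after less elapsed time in the treated arm, and in both arms at a shared functional milestone. Randomisation does not protect this comparison, because treatment itself helps to set the measurement time. A null or adverse result at full feeds could be taken as evidence against an NNS benefit when it partly reflects earlier measurement.

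**Working it through.** **The plan's own figure.** The protocol gives no sample size or power for NNS, only 105 per group for the primary outcome (5 days, SD 12, two-sided 0.05, 80% power). Normal approximation: n = 2 × (1.960 + 0.842)² × (12/5)² = 90.4, so 91; the exact t-test gives 92. Dividing by the Wilcoxon lower-bound efficiency of 0.864 gives about 106, and multiplying the t-test n (91.4) by 1.15 gives 105.1. So 105 reproduces. It is used below only as the number of infants available per arm.

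**Precision after training.** With 105 per arm, the unadjusted t-test has 80% power for (1.960 + 0.842) × √(2/105) = 0.387 SD. ANCOVA on one baseline value multiplies the residual variance by 1 − r², where r is the baseline–outcome correlation. That is equivalent to multiplying the sample by 1/(1 − r²). The protocol gives no r, so the range is assumed:

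| Assumed r | 1 − r² | Equivalent gain in infants | Infants per arm for the same power | Power for 0.387 SD |
|---|---|---|---|---|
| 0.3 | 0.91 | 10% | 96 | 83.6% |
| 0.5 | 0.75 | 33% | 79 | 89.9% |
| 0.7 | 0.51 | 96% | 54 | 97.5% |

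If two NeoSuckRT baselines exist and correlate with each other at the same r, the factor for their mean is 1 − 2r²/(1 + r) = 0.862, 0.667 and 0.424. Power is then 85.5%, 92.9% and 99.0%.

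If the t-tests were meant for change scores, the variance factor with equal variances would be 2(1 − r) = 1.4, 1.0 and 0.6. This exceeds 1 − r² at every value of r shown, so ANCOVA remains the better choice.

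**Timing at full feeds.** Inputs: a 5-day earlier event (Sample Size Calculation), taken as a 5-day age gap, which requires similar age at first oral feed in the two arms; and improvement in NNS with age at an assumed slope, since none is given. Shift against treatment = slope per week × 5/7. The last two columns use 105 per arm and the normal approximation.

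| Assumed slope (SD/week) | Shift (SD) | A same-age benefit of 0.387 SD appears as | Chance of showing that benefit | Rejection rate if there is no same-age effect |
|---|---|---|---|---|
| 0.10 | 0.07 | 0.32 SD | 63% | 8% |
| 0.25 | 0.18 | 0.21 SD | 33% | 25% |
| 0.50 | 0.36 | 0.03 SD | 4% | 74% |

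Without the shift, the fourth column would be 80%. The rejections in the last column fall almost entirely against the device. The table shows how the shift scales with the slope; it does not estimate the shift in this trial.

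**The case against.** **The t-test after training is valid.** This stands. In a randomised comparison the loss is precision on a secondary outcome, and its size rests on an assumed correlation. Covariates for secondary endpoints are often settled in the SAP, but here the protocol has itself named the test.

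**The text does not say whether raw values or changes are tested.** Also true, so one cannot be certain that baseline plays no part. No baseline term is stated, however, and a change-score t-test would still be less efficient than ANCOVA and would still omit the stratum.

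**Only one NeoSuckRT baseline is guaranteed.** Read narrowly, the two required assessments may be one clinical and one NeoSuckRT. The three-times-weekly schedule makes more likely, and one is enough.

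**The named hypothesis is not tested at full feeds.** A reader might infer that the secondary hypothesis on NNS is itself tested with bias. The Hypothesis section does not support that: it places the NNS benefit at completion of training. The full-feeds comparison is an additional look.

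**The 5 days is not an age difference.** A reader might infer that treated infants will be exactly 5 days younger at full feeds. The planning figure is an interval from first oral feed, and it becomes an age gap only if age at first oral feed is similar between arms.

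**NNS at a functional milestone is a legitimate question.** It is, but a different one, and the protocol does not say that this is what it estimates. The protocol applies similar caution elsewhere: for apnea, bradycardia and desaturation before discharge it doubts that testing is warranted, because those values are closely linked to the discharge decision.

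**Conclusion.** The point holds in a limited form. The post-training t-tests are sound but inefficient: adjustment for one baseline value is worth 10%, 33% or 96% more infants at an assumed r of 0.3, 0.5 or 0.7. The comparison at full oral feeds cannot be read as a same-age NNS effect and would tend to understate one, provided NNS improves with age and age at first oral feed is similar between arms. Its size is unknown, because the protocol gives no maturation slope.

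It would be tempting to repair the second comparison by adjusting for postmenstrual age at full feeds. That is not a remedy: this age is fixed after randomisation and is affected by treatment, so conditioning on it can introduce a bias of its own. The issue is confined to secondary outcomes and leaves the primary analysis untouched.

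**What to change.** 1. Make the comparison after completion of training, the time point already named in the Hypothesis section, the inferential NNS analysis. Analyse each parameter by ANCOVA with treatment, the pre-intervention NeoSuckRT value (the mean if there are several) and GA stratum.
2. Define that assessment as a fixed number of days from the start of training, or a fixed postmenstrual age, taken from the serial NeoSuckRT records. Held and restarted sessions otherwise let the age at completion vary between infants.
3. State what happens for infants who reach full oral feeds before that point, since the NeoSuckRT series is scheduled only until the primary outcome.
4. Report NNS at full oral feeds descriptively by arm, alongside postmenstrual age at that assessment, with no test and no adjustment for that age.

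The cost is mainly analysis wording. The baseline and serial records are already collected and the strata are known. The only possible addition is one NeoSuckRT recording for infants who reach full feeds before the fixed assessment, if the sponsor wants that value complete.
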